#### Pain

A range of pain scales are utilized to measure pain intensity (assessed by child, nurse, or parent). The Faces Pain Scale-Revised (FPS-R) [49] is used to assess the child’s self-report of pain and will be the primary outcome measure. Convergent validity of the FPS-R is supported by a strong positive correlation (*r* = 0.93, *p* < 0.001, *N* = 76) with a visual analog scale (VAS) pain intensity measure in children aged 5–12 years and by strong positive correlations with the VAS (*r* = 0.92, *p* < 0.001, *N* = 45) and the color analog scale (*r* = 0.84, *p* < 0.001, *N* = 45) in a clinical sample of pediatric inpatients aged 4–12 years [49]. Even among the youngest patients sampled (four-year-olds), there is evidence of usage of the FPS-R and analog scales in a consistent and reliable manner [49]. Nurses report a behavioral/observational rating on the Face, Legs, Arms, Cry, Consolability (FLACC) scale [50, 51]. The FLACC scale has been validated for use in settings such as postoperative pain [50]. Despite a recent systematic review rescinding recommendation of the FLACC scale for procedural pain assessment [51], we have chosen this scale in the absence of an acceptable alternative due to its extensive use in prior clinical trials examining procedural pain. Parents also rate their child’s pain using an 11-point (0 to 10) numeric rating scale (NRS) [52]. Pain scores reported verbally by the parent (NRS) and child (FPS-R) are documented by the primary investigator. Nurses document the FLACC pain scores.

#### Wound healing

Re-epithelialization is defined as ≥95 % wound healing and no further wound dressings required. Scabs or crusts are defined as unhealed areas [53]. For the purpose of the main analysis, this outcome measure will be assessed using the percentage re-epithelialization assessed from 3D digital photography by an independent surgeon and nurse blinded to study treatment group. The percentage re-epithelialization reported by the independent surgeon will be used in the main analysis if appropriate. The outcome will also be measured from 3D digital photography by the investigator ([name]), and the time to wound healing recorded in the medical records will also be used for comparative purposes. Wound photographs are taken at each dressing change using 3D LifeViz System™ (Quantificare, Sophia Antipolis, France) [54]. The independent blinded surgeon and nurse will mark out the wound edges after the photographs are taken, along with any unhealed areas. Surface area computer mapping will then be used to determine percentage re-epithelialization [53, 54].

#### Secondary outcome measures

Secondary outcome measures collected at baseline include a self-reported procedural anxiety measure, a saliva sample (for measurement of stress biomarkers: salivary cortisol and salivary α-amylase), and heart rate (HR). Baseline measurements are taken before nurses administer pharmacological analgesia according to PLPBC standard practice.

#### Procedural anxiety

The visual analog scale for anxiety (VAS-A) [55, 56] will be used to measure procedural anxiety in children. Self-reported anxiety measures will only be administered to children 8 years old and above. For participants younger than 8 years, the parent will be asked to assess their child’s anxiety using the same scale. The anxiety measurement is obtained prior to premedication and immediately after new dressing application.

#### PTSD

PTSD severity three months following injury will be assessed using the Child PTSD Symptom Scale (CPSS) [57] for children aged 7 years or older. The CPSS is designed to assess PTSD diagnosis and symptom severity in children ages 8 to 18 who have experienced a single-incident traumatic event [57]. Total symptom score and the three symptom clusters of the CPSS demonstrate high internal consistency (α = 0.89 for total score) [57]. The percentage agreement between PTSD diagnoses at two separate time points was 84 %, indicative of moderately high reliability [57]. Test-retest reliability of the total CPSS score is acceptable (κ = 0.84) [57]. Convergent validity of the CPSS has been supported (Pearson’s *r* = 0.80, *p* < 0.001) when measured against the Child PTSD Reaction Index (CPTSD-RI) [57].

The Young Child PTSD Checklist (YCPC) [58] will be used for children younger than seven years old. Face validity of the YCPC items is excellent based on a series of studies by Scheeringa et al. that used these items in an interview format and formed the basis for the new DSM-5 disorder titled “Posttraumatic stress disorder for children six years and younger” [59–62]. The test-retest reliability (intraclass correlation coefficient = 0.87) [63] was acceptable, and the predictive validity [64] of PTSD symptoms using an interview format has been supported.

#### Parent satisfaction

Ease of the child’s wound care procedure as assessed by the parent is a secondary outcome measure. At the conclusion of every dressing change, a parent rates how easy they believe the wound care procedure was for their child on a 5-point Likert scale (from “not at all easy” to “extremely easy”) with higher values indicating greater satisfaction.

#### Biochemical stress markers

Salivary cortisol, representing hypothalamic-pituitary-adrenal axis activity, and salivary α-amylase (a proxy for norepinephrine indicative of sympathetic adrenomedullary system activity) are measured as biomarkers of stress associated with wound care procedures [65]. The participant places a Salivette™ (Sarstedt Australia Pty., Ltd. Mawson Lakes, SA, Australia) under their tongue for 2 minutes for saliva collection at these times: (1) immediately before premedication prior to removal of wound dressing in clinic, (2) immediately after the new dressings are in place, and (3) three months post-injury to obtain a baseline. The parent completes a saliva collection survey which records variables pertinent to salivary analysis: collection time, time participant last woke up, time participant last brushed teeth, any medication given, any food/drink/gum during the previous hour, time participant last had any caffeine, and pertinent smoking or tobacco history.

The date, time, and volume of saliva collection are recorded in the laboratory and samples are refrigerated at 4 °C and processed within 7 days. Samples are spun in a centrifuge at 1400 × *g* at room temperature for 10 minutes and the saliva frozen at −80 °C until analysis. Salivary cortisol and α-amylase will be quantified using ELISA kits (Stratech Scientific, Avalon, NSW, Australia) with saliva samples analyzed in triplicate. Heart rate will also be recorded as a physiologic measure of pain and distress at time points (1) and (2) for each dressing change.

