### Participant timeline

Participants are enrolled after presenting to the PLPBC and after their study eligibility has been assessed (Fig. 1). Regardless of which trial arm they are randomized into, all participants receive treatment during their scheduled appointment times for burn wound care at the PLPBC. Primary outcome data is collected concurrently with participants’ scheduled wound care procedures until the burn wound is ≥95 % re-epithelialized. The endpoint for secondary outcome data collection is 3 months post-burn. No extra participant visits to the PLPBC are required for the sole purpose of data collection.

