### Data analysis

Data will be analyzed using SPSS 23 (IBM Corporation, Armonk, NY, USA). Descriptive statistics such as the mean and standard deviation, median and interquartile range, and confidence intervals will be used to report the sample demographics (i.e., age, gender, and mechanism of injury) and to summarize outcome measures, as appropriate. Between-group comparisons will be conducted for potential confounding variables for the primary outcomes. Potential confounding variables affecting wound healing that will be examined include burn depth, days taken to present to the PLPBC, ethnicity, mechanism of injury, percent TBSA, age, and gender [25]. Potential confounding variables affecting pain intensity that will be examined include age, the presence/absence of skin grafting, state anxiety (determined by VAS-A), pharmacologic analgesia given immediately before or during wound care procedures, percent TBSA, and days to re-epithelialization [26, 68]. If significant between-group differences are present for potential confounding variables, those variables will be controlled for in the primary analyses. Between-group differences will be investigated using univariate parametric or non-parametric analyses as applicable (e.g., linear regression, Student’s *t* test, or Mann-Whitney *U* test for continuous data and the chi-squared test or Fisher’s exact test for categorical data). All data will be analyzed on the intention-to-treat (ITT) principle as the primary approach. However, a sensitivity analysis will be conducted for data collected as per protocol. A repeated measures analysis will be undertaken using generalized estimating equations (GEEs) [69] including the main effect of treatment group and time on the primary pain and healing outcomes, as well as on the secondary outcomes of procedural anxiety, PTSD, parent satisfaction, and biochemical stress markers.

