Analyses will be conducted with data stratified for burn depth (superficial partial-thickness/deep partial-thickness/full-thickness) and participant age (e.g., <8 years/≥8 years, with age strata based on age-group validity of the VAS-A) [69]. Differences in hypnotic responsivity between the intervention group and a normative comparison group will be analyzed using z-scores or using equivalent non-parametric tests such as the Mann-Whitney *U* test where applicable. Differences in re-epithelialization by the independent blinded raters (surgeon and nurse) and the investigator ([name]) will be examined using reliability coefficients and measures of agreement (e.g., percentages of exact agreement). Differences between measures of pain (e.g., observer report by parents versus child self-report) will be examined using correlational analyses where appropriate.

The influence of demographic and clinical factors, and primary and secondary outcomes not included as dependent variables, on primary and secondary outcomes will be examined using regression models and GEE models. Post hoc adjustment for multiple comparisons will be conducted using the Šidák correction [70] where appropriate. Statistical significance will be set at *p* < 0.05.

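### The protocol records clock time and time since waking for each saliva sample but does not name them in the cortisol and alpha-amylase models, so available precision on this secondary outcome is not secured

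*Protocol article*

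**What the plan says.** Under Biochemical stress markers, saliva is collected before premedication, after the new dressing is on, and three months after injury. A parent survey accompanies collection: "The parent completes a saliva collection survey which records variables pertinent to salivary analysis: collection time, time participant last woke up". It also covers tooth brushing, medication, recent food, drink or gum, caffeine and smoking.

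No hour of sampling is set. Under Participant timeline, "all participants receive treatment during their scheduled appointment times for burn wound care at the PLPBC", and the dressing-change samples are tied to those procedures.

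The Data analysis section plans "generalized estimating equations (GEEs) [69] including the main effect of treatment group and time on the primary pain and healing outcomes" and extends this model: "as well as on the secondary outcomes of procedural anxiety, PTSD, parent satisfaction, and biochemical stress markers". The same section restricts its confounder work: "Between-group comparisons will be conducted for potential confounding variables for the primary outcomes". It then gives the adjustment rule: "If significant between-group differences are present for potential confounding variables, those variables will be controlled for in the primary analyses". One list of candidate confounders is for wound healing and one is for pain. Neither contains sampling time or time since waking.

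Later in the section, the influence of demographic and clinical factors, and of other outcomes, "on primary and secondary outcomes will be examined using regression models and GEE models".

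**The concern.** The protocol takes the trouble to collect variables that it regards as relevant to interpreting saliva, and then states a biomarker model that does not mention them. Sampling follows the wound-care appointment, so the hour can differ between children and between visits. Any part of cortisol or alpha-amylase that moves with the clock or with time since waking then stays in the residual.

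With about 33 children per arm, the confidence interval for the stress-marker hypothesis may be wider than the collected data require. Leaving the covariates unnamed also leaves the choice open until the data have been seen.

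**Working it through.** **1. The plan's own sample-size figure.** The Sample size section uses a 3-day difference, SD 4, alpha 0.05 and 80% power. Sidedness is not stated; two-sided is assumed here.

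- Normal approximation: n = 2 × (1.960 + 0.842)² × (4/3)² = 27.9, so 28 per group.
- Two-sample t test: 28.9, so 29 per group, as stated.
- 10% loss: 29/0.9 = 32.2, so 33 per group and 66 in total, as stated.

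The figure reproduces. It concerns healing; the article gives no sample size or power for the biomarkers.

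**2. Where the timing variables could enter the analysis.**

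| Part of Data analysis | Covers the biomarkers? | Names clock time or time since waking? |
|---|---|---|
| GEE with group and time | Yes | No |
| Confounder lists | No (healing and pain only) | No |
| Adjustment rule | No (primary analyses only) | No |
| Further regression and GEE models | Yes, as secondary outcomes | No; demographic and clinical factors |

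The section headed Demographic and clinical information shows what the last row plainly includes: injury mechanism and site, burn area, depth, first aid and medication. Only medication overlaps with the saliva survey. In the GEE, time is most naturally read as measurement occasion, not hour of day.

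**3. Does the repeated-measures structure remove clock time?** Take one visit, with a child-specific level a, a timing contribution b·t shared by the two samples, and errors e1 and e2.

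- Within-visit change: (a + b·t + e2) − (a + b·t + e1) = e2 − e1. The timing term cancels to the extent that it is shared.
- Average level, which a group main effect compares: a + b·t + (e1 + e2)/2. The timing term remains.

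The stated effect is a group main effect, so differences in timing between children are not cancelled. The three-month sample falls on another day, so a change from that sample would not cancel them either.

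**4. Size.** Let R² be the share of variance in biomarker level explained by the two timing variables. The documents give no value; 0.05 to 0.40 is assumed. For a simple two-group comparison with 33 per arm:

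- SE ratio, adjusted to unadjusted = √(1 − R²)
- Detectable standardized difference at 80% power = 0.70 × √(1 − R²)
- Unadjusted size giving the same precision = 33/(1 − R²)
- Power is shown for an assumed true difference of 0.5 SD

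| R² | SE ratio | SE reduction | Detectable difference (SD) | Equivalent n per arm | Power at 0.5 SD |
|---|---|---|---|---|---|
| 0 | 1.000 | 0 | 0.70 | 33.0 | 52% |
| 0.05 | 0.975 | 2.5% | 0.68 | 34.7 | 54% |
| 0.10 | 0.949 | 5.1% | 0.66 | 36.7 | 56% |
| 0.20 | 0.894 | 10.6% | 0.63 | 41.2 | 61% |
| 0.30 | 0.837 | 16.3% | 0.59 | 47.1 | 67% |
| 0.40 | 0.775 | 22.5% | 0.54 | 55.0 | 73% |

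By step 3, the gain for a within-visit change is smaller than the table shows.

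**The case against.** The strongest objection is that this is a condensed article whose SAP is not shown, and covariates for one family of secondary outcomes are normally left to that document. Silence alone would indeed not be a point. Here, however, the article names the biomarker model and writes an adjustment rule confined to the primary outcomes. Someone following that text would have no instruction to use the timing data.

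Three stronger readings are tempting, and the documents support none of them.

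- **The biomarkers are modelled with group and time and nothing else.** The text says the model includes these effects, which is not exhaustive. Further models for secondary outcomes are planned, and medication, a survey item, falls among the clinical factors. No passage says that the timing data will go unused.
- **The comparison is biased by appointment times.** Allocation is random. Chance imbalance is possible with simple randomization of 66 children, but the standard error already allows for it, so it is not bias.
- **A known share of the sample is wasted.** The R² range is assumed, one range is applied to two different markers, and the article gives neither clinic hours nor the spread of appointment times. The formula describes independent observations compared between two groups, not the full repeated-measures design.

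A further objection concerns the remedy. Post-procedure collection time comes after treatment has begun and depends on procedure length, which hypnosis could change. Adjusting for it would need its own justification. This objection stands, and it determines which time the fix uses.

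**Conclusion.** The point holds as one about precision on a secondary outcome. The article collects clock time and time since waking as relevant to the saliva analysis, names neither in the GEE it states for the stress markers, and limits its adjustment rule to pain and healing. A group main effect on levels does not remove timing differences between children, so the available precision is not secured.

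Under an assumed R² of 0.05 to 0.40, the gain runs from slight (2.5% off the standard error) to material (22.5%) for a comparison of levels. The true value may lie at the low end. The primary outcomes and the sample size are unaffected.

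**What to change.** Before the data are locked, state that the cortisol and alpha-amylase models include two pre-specified covariates: the clock time, and the time since waking, at each visit's pre-procedure sample. The post-procedure time should not be used. Time since waking is the recorded collection time minus the recorded time last awake.

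Add a sensitivity analysis that leaves out samples flagged for food, drink or gum in the previous hour or for recent caffeine. The survey records only when caffeine was last taken, so the window that counts as recent must be fixed in advance.

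The cost is a few sentences of analysis text and about two degrees of freedom if both covariates enter linearly. Every variable is already on the survey, so no new data are needed.

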#### Hypnotic responsivity

The Stanford Hypnotic Clinical Scale for Children (SHCS-C) [66] will be used to assess and record hypnotic responsivity for participants in the intervention group as recommended by prior methodological reviewers of relevant literature [32]. This assessment will only be conducted within the intervention group to ensure that control participants remain naïve to hypnotherapy. Normative data for hypnotic responsivity are available for children aged 3–16 years. The SHCS-C correlated 0.67 with a slightly modified version of the Stanford Hypnotic Susceptibility Scale, Form A for pediatric use [66], supporting concurrent validity.

### Demographic and clinical information

Participant demographics and medical history are recorded from the caregiver and hospital chart: mechanism and site of injury, estimated percentage total body surface area (TBSA) of burn, burn depth, any first aid treatment applied, and medication given. TBSA is determined by a consultant surgeon using the Lund and Browder method [67].

### Participant timeline

Participants are enrolled after presenting to the PLPBC and after their study eligibility has been assessed (Fig. 1). Regardless of which trial arm they are randomized into, all participants receive treatment during their scheduled appointment times for burn wound care at the PLPBC. Primary outcome data is collected concurrently with participants’ scheduled wound care procedures until the burn wound is ≥95 % re-epithelialized. The endpoint for secondary outcome data collection is 3 months post-burn. No extra participant visits to the PLPBC are required for the sole purpose of data collection.

### Sample size

A sample size estimate was derived from the primary outcomes: days to re-epithelialization and pain. Based on re-epithelialization within 15 (SD = 4) days and a minimum clinically important difference (MCID) of 3 days [26], the sample size required was estimated as 29 per group, using 80 % power and an α of 0.05. Allowing for 10 % loss to follow-up, a total of 66 participants will be required. Additionally, this sample size is adequate to show an MCID of 2 (SD 2.5) in the pain outcome measures [26]. Recruitment will continue until at least 33 participants in each arm have been obtained with complete data for the primary outcomes.

### Randomization

A computerized random number generator is used to randomize study participants. Simple randomization is overseen by staff not involved with the study. Third-party concealment of group allocation occurs by using a numbered series of opaque, sealed envelopes prepared in advance. The primary researcher is then told to which group the participant is allocated.

### Blinding

Medical hypnosis provided throughout a procedure cannot be masked. This study’s nature prevents full blinding, but certain outcome measures are blinded. The re-epithelialization assessors are blinded, as these measurements take place using 3D digital photographs. Trial group allocation remains unknown to this assessor. If discrepancy arises between the two re-epithelialization assessors, the assessment of the blinded assessor is taken as definitive to reduce potential performance bias. Burn depth and salivary analysis are also blinded measures, as data for these variables are provided to the investigators in a non-identifiable format and as the assessor of these variables is blinded to trial group allocation.

### Discontinuation

Study participants can withdraw from the trial at any time. The number of adverse events will be documented, and any adverse event will be described in detail for both treatment groups. Current relevant literature has not reported any serious harmful effects associated with indicated pediatric medical hypnosis or hypnotherapy.

### Data analysis

Data will be analyzed using SPSS 23 (IBM Corporation, Armonk, NY, USA). Descriptive statistics such as the mean and standard deviation, median and interquartile range, and confidence intervals will be used to report the sample demographics (i.e., age, gender, and mechanism of injury) and to summarize outcome measures, as appropriate. Between-group comparisons will be conducted for potential confounding variables for the primary outcomes. Potential confounding variables affecting wound healing that will be examined include burn depth, days taken to present to the PLPBC, ethnicity, mechanism of injury, percent TBSA, age, and gender [25]. Potential confounding variables affecting pain intensity that will be examined include age, the presence/absence of skin grafting, state anxiety (determined by VAS-A), pharmacologic analgesia given immediately before or during wound care procedures, percent TBSA, and days to re-epithelialization [26, 68]. If significant between-group differences are present for potential confounding variables, those variables will be controlled for in the primary analyses. Between-group differences will be investigated using univariate parametric or non-parametric analyses as applicable (e.g., linear regression, Student’s *t* test, or Mann-Whitney *U* test for continuous data and the chi-squared test or Fisher’s exact test for categorical data). All data will be analyzed on the intention-to-treat (ITT) principle as the primary approach. However, a sensitivity analysis will be conducted for data collected as per protocol. A repeated measures analysis will be undertaken using generalized estimating equations (GEEs) [69] including the main effect of treatment group and time on the primary pain and healing outcomes, as well as on the secondary outcomes of procedural anxiety, PTSD, parent satisfaction, and biochemical stress markers.

Analyses will be conducted with data stratified for burn depth (superficial partial-thickness/deep partial-thickness/full-thickness) and participant age (e.g., <8 years/≥8 years, with age strata based on age-group validity of the VAS-A) [69]. Differences in hypnotic responsivity between the intervention group and a normative comparison group will be analyzed using z-scores or using equivalent non-parametric tests such as the Mann-Whitney *U* test where applicable. Differences in re-epithelialization by the independent blinded raters (surgeon and nurse) and the investigator ([name]) will be examined using reliability coefficients and measures of agreement (e.g., percentages of exact agreement). Differences between measures of pain (e.g., observer report by parents versus child self-report) will be examined using correlational analyses where appropriate.

The influence of demographic and clinical factors, and primary and secondary outcomes not included as dependent variables, on primary and secondary outcomes will be examined using regression models and GEE models. Post hoc adjustment for multiple comparisons will be conducted using the Šidák correction [70] where appropriate. Statistical significance will be set at *p* < 0.05.

